### Secondary outcome measures for the SSHeW trial

Secondary outcomes will be self-reported by the participant and collected via text or questionnaires sent at baseline, 14 weeks or following the report of the first slip or an injury. They include:The incidence rate of falls resulting from a slip in the workplace over 14 weeks.The incidence rate of falls not resulting from a slip in the workplace over 14 weeks.Proportion of participants who report a slip over 14 weeks.Proportion of participants who report a fall over 14 weeks.Proportion of participants who report a fracture over 14 weeks (numbers permitting).Time to first slip.Time to first fall.EuroQol EQ5D-5L.Cost-effectiveness.

Other important information collected includes:Reason for slip/fall, location of fall, type of flooring and if wet or dry, consequence of slip/fall, that is, superficial wound (bruising sprain, cut, abrasions), fractures and type of fractures; severity of fall; type of footwear worn at time of slip/fall.Number of days off work, due to the slip or fall.Footwear worn at time of first slip.Number of hospital admissions.Number of days in hospital.Compliance and reasons for non-compliance.Any minor injuries resulting from ill-fitting shoes.Style of footwear usually worn.Wear on soles of 45 intervention shoes at 6, 9 and 12 months postrandomisation.Slip resistance of a sample of the current footwear worn by NHS staff.

Copies of the data collection forms are available from the corresponding author.

### Nested qualitative study

Qualitative interviews will be undertaken in order to determine the acceptability of the footwear. The reasons for wearing or not wearing the footwear and views on the impact of the footwear including unintended consequences will be explored. For instance, there may be certain staff groups for whom it is difficult to store the footwear at work (eg, absence of personal lockers). We will also interview relevant health service managers, at least one per site, regarding the contextual influences on the use of the footwear. We will purposively select a sample of 30–40 intervention participants, who have completed follow-up and are a mix of partial and non-adherers (as indicated by their follow-up data) across clinical (eg, nursing/medical staff) and non-clinical specialties (eg, cleaning/portering staff) for a brief telephone interview. The maximum variation sampling approach will ensure a collection of a wide range of views.^7^ Interviews will be conducted using a topic guide to ensure consistency, although the format will be flexible in order to allow participants to generate naturalistic data on what they see as important.

### Adverse events

This study will record and report only details of any serious adverse events (SAEs) that are required to be reported to the Health Research Authority (HRA), that is, events which are related to taking part in the study and are unexpected. Non-SAEs will not be recorded or reported for this study unless they are related to being in the study or are related to the intervention. The adverse event reporting period for this trial begins as soon as the participant consents to be in the study and ends approximately 14 weeks after they are randomised, that is, after they are sent their final data collection text message. Adverse events will continue to be collected for participants who agree to long-term follow-up. For those participants who are not randomised, the reporting period will end once the participant is informed that their participation in the study has ended.

The most common adverse event likely to occur within this study relates to falls and slips, which are being recorded as an outcome measure of the trial. If a participant has a fall or slip, an adverse event form will not be completed as data are collected elsewhere.

For this trial an SAE is defined as any untoward occurrence that:Results in death;Is life threatening;Requires hospitalisation or prolongation of existing hospitalisation;Consists of a congenital anomaly or birth defect;Is otherwise considered medically significant by the investigator.

It is expected that some participants may experience minor injuries, resulting from ill-fitting shoes. This may include: blisters, corns, calluses, foot pain, athlete’s foot, ingrown toe nails and general foot pain/discomfort. Occasionally, ill-fitting shoes can cause more persistent foot complaints such as: plantar fasciitis, Morton’s neuroma, bursitis or capsulitis, which can present as pain, swelling and sometimes numbness in the toes. Structural changes over time can also occur from ill-fitting footwear, for example, flat foot or toe deformities such as retracted/hammer/claw/mallet toes and bunions. It is worth noting that the participant may also already have these foot deformities and the shoe style will need to accommodate their altered foot shape. If they are not easily accommodated with the appropriate style of shoe, we can expect that minor injuries will occur and discontinuation of the footwear will be required.

It is expected that some participants will slip, trip or fall during the trial. As a result of such events, participants may require medical treatment, for example, treatment of sprains, damage to ligaments, tendons or muscles, or fractures and may require time off work. In rare cases, participants may require hospitalisation or in extremely rare cases, may be permanently injured or die as a result of a fall or slip. It is also expected that there may be incidents of hospitalisations, illnesses, disabling/incapacitating/ life-threatening conditions, ageing-associated diseases (such as cancer, cardiovascular disease, diabetes, arthritis, osteoporosis, dementia) and other common illnesses such as depression, and rarely deaths in the study population, such events which are deemed unrelated to the study will not be reported.

An event is defined as ‘related’ if the event was due to the administration of any research procedure. An ‘unexpected event’ is defined as a type of event not listed in the protocol as an expected occurrence. The relatedness and expectedness of an event will be reviewed by the Chief Investigator and the TSC.

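### Serious adverse events must be related and unexpected to be recorded, non-serious ones only related, so a related serious event of a listed type drops out of the adverse event record

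*Protocol article*

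**What the plan says.** All the governing text is in the Adverse events section of the protocol article.

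- **Serious events.** The study will "record and report only details of any serious adverse events (SAEs) that are required to be reported" to the HRA, and the article explains which these are: "that is, events which are related to taking part in the study and are unexpected". Both recording and reporting fall under this restriction.
- **Non-serious events.** "Non-SAEs will not be recorded or reported for this study unless they are related to being in the study or are related to the intervention". No test of expectedness is applied.
- **Seriousness.** One criterion is that the event "Requires hospitalisation or prolongation of existing hospitalisation".
- **Unexpected.** This is defined as a "type of event not listed in the protocol as an expected occurrence". The section lists foot complaints from ill-fitting shoes, consequences of slips and falls, and general illness in the workforce.
- **Related.** An event is related if "the event was due to the administration of any research procedure".
- **Review.** "The relatedness and expectedness of an event will be reviewed by the Chief Investigator and the TSC".

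Slips and falls are kept off the adverse event form because they are captured as outcomes. Separately, the section on secondary outcome measures lists hospital admissions, days in hospital and minor injuries from ill-fitting shoes among the other information collected. The Secondary analysis section says such data will be summarised overall and by arm.

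**The concern.** Expectedness normally decides which related serious events need onward reporting. Here it also decides whether a serious event is recorded at all, while non-serious events face no such test. For a listed event type, the threshold for entering the record therefore rises as the event becomes serious.

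What is at stake is the reading of the safety results. The Introduction says the findings will inform employers' risk assessments and the business case for buying this footwear. Those readers will want to know whether the shoes caused any serious harm. If a related serious event of a listed type cannot enter the record, a count of zero does not answer that question. The efficacy comparison is not affected.

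**Working it through.** The documents give no event rate and the point rests on no calculation. The check applies the two recording rules to each kind of event.

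**Step 1: the rules as conditions.**

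- SAE recorded if: related AND of a type not listed as expected.
- Non-SAE recorded if: related to the study OR to the intervention.

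**Step 2: apply them to events that are not slips or falls.**

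| Serious? | Related? | Type listed as expected? | In the adverse event record? |
|---|---|---|---|
| No | Yes | Yes (e.g. a blister) | Yes |
| No | Yes | No | Yes |
| Yes | Yes | No | Yes |
| Yes | Yes | Yes (e.g. a listed foot complaint leading to admission) | **No** |
| Either | No | Either | No |

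Rows 1 and 4 differ only in seriousness. Becoming serious removes the event from the record.

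**Step 3: can row 4 occur?** The listed shoe effects are in three groups: minor injuries, more persistent complaints (bursitis and plantar fasciitis among them), and structural changes over time. A case in any group that led to admission would meet the hospitalisation criterion and would still be of a listed type.

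**Step 4: would row 4 be captured elsewhere?**

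- The shoe-injury item among the other information is limited to minor injuries, so it does not clearly cover a serious one.
- Admissions and hospital days are self-reported and will be shown by arm, so the admission may be visible there. The article does not say whether these items are limited to slips and falls, and it states no causality assessment for them. A shoe-related admission would not be identifiable as a related SAE.
- A serious consequence of a slip or fall is captured as outcome data and is outside this gap.

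**Step 5: is relatedness worded consistently?** The section uses three wordings. The SAE rule refers to taking part in the study, the non-SAE rule to the study or the intervention, and the definition to a research procedure. Only the non-SAE rule names the intervention.

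**The case against.** The strongest case on the other side is that little is really lost. Related, unexpected SAEs are recorded. The most foreseeable serious events, injury or admission after a slip or fall, are deliberately collected as outcomes. Admissions are summarised by arm, and the qualitative study explores unintended consequences of the footwear. All of this stands, and it limits the point to row 4. A reader might infer that the trial omits its worst related harms; the documents do not support that.

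Three other strong readings also fail:

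- **That every related admission is excluded because hospitalisations are named as expected.** That sentence concerns background events in the study population, and its stated exclusion covers only those judged unrelated.
- **That the Chief Investigator and the Trial Steering Committee (TSC) never see the filtered events.** The article does not describe how events reach them, and a review of relatedness and expectedness suggests that events are seen before they are classified. What the text lacks is any requirement to keep a record of a related serious event once it is judged expected.
- **That harm from the shoes falls outside the SAE rule by definition.** Taking part in the study can naturally include wearing shoes the trial supplies. The research-procedure definition leaves this unclear but does not settle it the other way.

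It can also be argued that an admission is a different type of event from the minor injury listed, so that the reviewers could call it unexpected. That is open to them, most plausibly for the group introduced as minor. The definition turns on type and does not mention severity, and the list goes beyond minor injuries. The rule as worded still points to exclusion.

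Finally, the trial is under way, so a change now would make capture uneven over time. That is a real cost, taken up in the fix.

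**Conclusion.** The point holds in a limited form. The article states a recording rule under which a related SAE of a listed type, not arising from a slip or fall, is left out of the adverse event record while its non-serious counterpart is included. This is a rule fixed badly, not detail left to a fuller document.

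The size cannot be computed because the documents give no rate. The described shoe effects are mainly minor or persistent foot complaints, so the number of such SAEs is probably small (an assumption). The planned 2200 intervention participants are the number to be offered shoes during follow-up, not the number expected to be affected.

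The conclusion rests on two readings of the text: that the restriction on recording means what it says, and that expectedness is judged by type whatever the severity. The consequence is one of interpretation: a report of no related SAEs could reflect the rule and not the absence of harm.

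**What to change.** 1. Reconcile the two recording sentences in the Adverse events section so that every SAE related to the study or the footwear is recorded, irrespective of expectedness.
2. Use expectedness only to decide which of these go to the HRA.
3. Align the definition of related with the non-SAE sentence, so that it explicitly covers the intervention as well as research procedures.
4. Have the Chief Investigator and the TSC classify from that record, and tabulate related SAEs by arm, split into expected and unexpected.

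The cost is a wording change and a few extra forms; the change to recording need not increase what is sent to the HRA. The main drawback is timing. The Trial status section says recruitment and follow-up are in progress, and the Pen substudy section says about 2000 participants had already completed follow-up when that substudy began. The report should therefore state the date from which the wider recording applied, so that readers do not treat the earlier period as fully covered.

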## Trial intervention

### SSHeW trial control group

Participants allocated to the control group will be asked to wear their usual work footwear for 14 weeks after they are randomised into the study. At the end of this period, they will be offered a free pair of slip resistant shoes provided by ’Shoes for Crews' and paid for by the Trust. It is possible that participants in the control group are already wearing what some would class as slip resistant footwear. The baseline questionnaire will request details of their current footwear style, brand and place of purchase, which will indicate if contamination of the control group has occurred. There is the potential for control group participants to purchase and wear the shoes being evaluated in the trial, as the footwear is commercially available. We believe the likelihood of this happening will be minimised by the fact that control participants will be offered a free pair of trial shoes when their participation in the study has ended. This information will be clearly stated in the study information sheet and control participants will be sent a text 8 weeks after randomisation, reminding them that they will receive their new ‘Shoes for Crews’ footwear at the end of follow-up.

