### Secondary analysis

All secondary outcomes and other important collected data will be summarised descriptively overall and by trial arm.

The incidence rate of falls (both resulting and not resulting from a slip) over 14 weeks will be analysed in the same way as described above for slips. The following outcomes will be analysed using a mixed effects logistic regression adjusting for the same covariates as the primary analysis and NHS trust as a random effect: (i) the proportion of participants who slip at least once over 14 weeks; (ii) the proportion of participants who fall at least once over 14 weeks and (iii) subject to a sufficient number of events, the proportion of participants who experience a fracture over 14 weeks. ORs and their associated 95% CIs will be provided.

Time to first slip and the time to first fall will be calculated. Participants who do not report a slip or fall will be treated as censored at their date of trial exit (completion of follow-up or withdrawal). The proportion of participants yet to experience a slip/fall will be summarised by a Kaplan-Meier survival curve for each group. Time to slip/fall will be analysed using Cox proportional hazards regression, with shared centre frailty and adjusting for the same covariates as in the primary analysis model. HRs and their associated 95% CIs will be provided. The proportional hazards assumption will be evaluated using Schoenfeld residuals.

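### The relatedness filter on non-serious events captures shoe-related foot problems unequally by arm and does not fit the protocol's own minor-injury item

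*Protocol article*

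**What the plan says.** Three parts of the protocol article bear on this point.

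**Adverse events.** The rule for non-serious events is: "Non-SAEs will not be recorded or reported for this study unless they are related to being in the study or are related to the intervention". An event counts as related "if the event was due to the administration of any research procedure". The section also says: "It is expected that some participants may experience minor injuries, resulting from ill-fitting shoes". It gives examples such as blisters and corns, then describes separately some more persistent complaints, such as plantar fasciitis and bursitis, and structural changes over time. For slips and falls it explains that no adverse event form is completed because those data arrive by another route. It says nothing similar about foot problems.

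**Control condition.** The section on the control group sets out what that arm wears during follow-up: "Participants allocated to the control group will be asked to wear their usual work footwear for 14 weeks after they are randomised into the study".

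**Secondary outcome measures and Secondary analysis.** The list of other important information includes "Any minor injuries resulting from ill-fitting shoes". The analysis text adds: "All secondary outcomes and other important collected data will be summarised descriptively overall and by trial arm".

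**The concern.** Foot problems are the main harm that the protocol itself expects from footwear, and ordinary work shoes cause them too. A fair comparison needs the same problem to be recorded in the same way whichever shoe caused it. A filter that depends on relatedness to the study or the intervention does not do this, because only one arm wears the intervention during follow-up.

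The open design adds to the difficulty. The Blinding section says that participants and the active study team are unblinded, and nobody can decide whether a foot problem came from a trial shoe without knowing which shoe was worn.

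At stake is the reading of any by-arm table of foot problems. The Introduction says the findings should inform employers' risk assessments and the business case for the footwear. A table fed by the filtered reports would tend to make the trial shoes look worse than usual footwear. A reader who noticed this and set the table aside might miss a real excess. The primary outcome is not affected.

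**Working it through.** The protocol states no figure on this point, so the check sets the passages side by side and follows the same foot problem through each recording route.

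| Foot problem | Route | Intervention arm, trial shoe | Control arm, own shoe |
|---|---|---|---|
| Minor, e.g. a blister | Adverse event report | Recordable: related to the intervention | Normally not: neither a research procedure nor the intervention caused it |
| Minor | Minor-injury item | Listed as collected | Listed as collected, no arm limit; form not shown |
| Persistent, non-serious | Adverse event report | Recordable | Normally not |
| Persistent, non-serious | Minor-injury item | Unclear whether it counts as minor | Unclear whether it counts as minor |

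**Unequal capture.** Controls are asked to keep wearing their usual shoes. A blister from those shoes would have arisen without the trial, so it is hard to call it related to being in the study. In the adverse event route the two arms differ.

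**Conflict.** For a control participant's blister, the adverse event rule says that it is not recorded, while the outcome list says that minor shoe injuries are collected. The section that exempts slips and falls from adverse event forms does not exempt foot problems, so the text leaves open which statement governs.

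**Gap.** The protocol separates persistent complaints from minor injuries. If the item covers only minor injuries, the filtered route is the only one left for non-serious persistent complaints. Serious event reporting does not fill the gap: it is limited to events that are both related and unexpected, and an unexpected event is one the protocol does not list as expected. These complaints are named in its account of expected shoe injuries.

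**Possible size (assumptions, not protocol figures).** Let p be the true risk of a shoe-related foot problem over 14 weeks, equal in both arms. Let capture be 100% in the intervention arm and a fraction c in the control arm.

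- Apparent risk ratio = p / (p × c) = 1/c, whatever p is.
- c = 0.75: 1/0.75 = 1.33
- c = 0.50: 1/0.50 = 2.0
- c = 0.25: 1/0.25 = 4.0
- c = 1 (equal capture): 1.0, the true value.

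The apparent risk difference is p × (1 − c). With p assumed to be 10%, it is 2.5, 5.0 and 7.5 percentage points for c of 0.75, 0.50 and 0.25. These figures apply to the adverse event route only.

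**The case against.** A reader might infer that control foot injuries are not captured at all, and that the trial cannot compare harm between the shoes. The protocol does not support that reading. The minor-injury item stands outside the Adverse events section and is not limited to one arm or to the trial shoes. Where the authors wanted such a limit in the same list, they wrote it: "Wear on soles of 45 intervention shoes at 6, 9 and 12 months postrandomisation". A summary by arm presupposes data from both arms. No passage says that the adverse event rule governs this item, and the handling of slips and falls shows that the protocol treats the two routes as separate. Secondary outcomes are self-reported by text or questionnaire, and the minor-injury item may well be collected in the same way. The forms are not shown, so an identical question may already go to both arms.

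It is also fair to say that limiting non-serious reports to related events is a common choice of scope, that no objective or formal comparison concerns foot injuries, and that any figure for the bias has to be assumed.

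Most of this stands, and it limits the point. It does not remove it. The adverse event rule is written without an exception for foot problems and conflicts with the item for controls. The item follows the one on compliance, and the discussion of ill-fitting shoes turns to choosing a suitable style and to discontinuing the footwear, so a reading confined to trial shoes is plausible. The article does not say that both arms are asked the same question. Persistent complaints have no clear unfiltered route.

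**Conclusion.** The point holds in a limited form. Adverse event reporting, as written, captures non-serious shoe-related foot problems unequally by arm, and its counts cannot support a comparison of foot harm. The rule needs to be reconciled with the outcome list, and the place of persistent complaints needs to be stated.

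The size is unknown. The apparent risk ratios of 1.33 to 4.0 rest on equal true risk, full capture in the intervention arm and control capture of 75% down to 25%, none of which the protocol supplies. The extreme case, with nothing recorded in the control arm, should not be assumed for the trial as a whole, because the minor-injury item offers controls a route. If the forms already put the same question to both arms and cover persistent complaints, only the wording of the protocol and the choice of data source for the harm table are at issue.

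**What to change.** 1. In the Adverse events section, exempt foot problems from the relatedness filter and say that they are collected by questionnaire, as the section already does in substance for slips and falls. Keep the filter for other non-serious events.
2. State that one identically worded item in the 14-week questionnaire asks both arms about any new or worse foot problem, minor or persistent, from whatever shoes were worn at work since randomisation. The questionnaire appears to go to both arms already, since the pen substudy built on it adjusts for main trial allocation.
3. Base the by-arm descriptive summary on that item, and state that adverse event form counts will not be compared between arms.
4. If the current forms do not already do this, add the item for participants still to reach 14 weeks (the Trial status section says follow-up was in progress) and report how many in each arm were asked.

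The cost is a protocol wording change, one questionnaire item and slightly more data entry. The comparison would still be unblinded self-report, and the text should say so.
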